#### Subgroup analyses

The primary outcome will be compared in the intention-to-treat cohort only, in the following a-priori-defined subgroups using a chi-square test (Additional file 1: Table S5). Results will be reported using RR and 95% CI and the multivariable logistic regression will be used to report the results of tests of interactions for these subgroups:UFH and LMWH. Randomization is stratified according to the type of heparin as it may modify the protective effect of IPC on DVT, especially in trauma patients for whom LMWH may be more effective than UFHFemoral CVC at baseline and no femoral CVC at baseline. IPC may have preferential effect in patients with femoral CVC by reducing venous blood stasis. In addition, patients with femoral CVC may have higher baseline rate of DVT, and therefore IPC effect may varyTrauma, postoperative and medical admission diagnoses. IPC may have differential effects on these groups as they have different baseline risksHeart failure and no heart failure (NYHA classification grades III and IV). IPC may have differential effects on these groups as they have different baseline DVT risksEjection fraction of < 40% or ≥ 40%. This cutoff has been used in several clinical trials to define heart failure with preserved ejection fraction [15–17]. IPC may have differential effects on these groups as they have different baseline DVT risksBMI < 30 and BMI ≥ 30. Given that obesity is a risk factor for DVT, IPC may have differential effects according to BMIVasopressors versus no vasopressors. Patients on vasopressors are at increased risk for DVT; therefore, IPC may have differential effects according to vasopressor therapy [18]Country: there are differences in patient populations and clinical practices that may influence the baseline DVT risk, including mobility and duration of stay in the ICU. Therefore, IPC may have differential effects according to the countryAbove-knee sleeves compared to control and below-knee sleeves compared to controlSequential devices compared to control and non-sequential devices compared to control

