**Methods/design:**

In this multicenter randomized trial, critically ill patients receiving pharmacologic thromboprophylaxis will be randomized to an IPC or a no IPC (control) group. The primary outcome is “incident” proximal lower-extremity deep vein thrombosis (DVT) within 28 days after randomization. Radiologists interpreting the lower-extremity ultrasonography will be blinded to intervention allocation, whereas the patients and treating team will be unblinded. The trial has 80% power to detect a 3% absolute risk reduction in the rate of proximal DVT from 7% to 4%.

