## Methods/design

### Study design

The PREVENT trial will enroll 2000 critically ill patients from 16 hospitals in 4 countries. The study has been approved by the Institutional Review Boards (IRBs) of the participating sites. The trial is registered at ClinicalTrials.gov: (NCT02040103) and Current Controlled Trials (ISRCTN44653506). The study is sponsored by King Abdulaziz City for Science and Technology (Grant number AT 65-34) and King Abdullah International Medical Research Center (Protocol number RC12/045/R), Riyadh, Saudi Arabia. The sponsors have no role in the study design, management or analysis.

All patients will be screened for eligibility within 48 h of ICU admission. Medical-surgical-trauma ICU patients, using accepted age cut-offs in participating adult ICUs (e.g. ≥ 14, 16 or 18 years), who weigh ≥ 45 kg, are expected to stay in ICU for ≥ 72 h and are eligible for pharmacologic thromboprophylaxis with either UFH and LMWH will be enrolled (Fig. 1). Exclusion criteria have been detailed in the protocol manuscript [5]. To enhance the generalizability of our findings, we permit the use of a broad array of IPC devices from various manufacturers intended for DVT prophylaxis. These devices include sequential devices (multi-chamber cuffs) and non-sequential devices (single-chamber cuff); the type of device will be recorded. IPC will be applied continuously for at least 18 h per day. The study intervention will continue for the duration of the ICU stay or up to 28 days after randomization; after which IPC use will be at the discretion of treating team. All enrolled patients will have a bilateral lower-extremity ultrasonography performed by a certified technologist at baseline (within 48 h of enrollment) and twice weekly thereafter until the diagnosis of a lower-extremity DVT or PE, ICU discharge, death, full mobility or 28 days (Fig. 2).

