### Intervention data

For each group we will report details regarding IPC use and the average daily duration of use (excluding study first and last days because they are usually less than 24 h, Additional file 1: Table S2). We will report reasons for not using IPCs in the IPC group and reasons for IPC use in the control group. We will classify these events as per-protocol and not per-protocol. We will classify IPC devices as sequential or non-sequential and will report the use of thigh- or knee-length sleeves and the use of foot pumps.

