### Statistical analysis

Categorical variables will be reported as numbers and frequencies, and will be compared using the chi-square test. Continuous variables will be reported as mean and standard deviation or median and interquartile ranges (IQR, Q1–Q3). Continuous variables will be tested using the Student’s *t* test or the Wilcoxon-Mann-Whitney test, as judged appropriate by normality testing. For serial measurements, we will test the change over time and the difference between the two groups over time using a repeated-measures analysis of variance, with no imputation for missing values. For serial measurements, we will use the Bonferroni correction to account for multiple comparisons. Associations will be reported as risk ratios (RR) or hazard ratios (HR) with 95% CIs. Unless otherwise specified, tests will be two-sided and at the 5% significance level. All statistical analyses will be conducted using the SAS software version 9.1.3 or higher (SAS Institute, Cary, NC, USA).

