#### Interim analyses

In making a decision to recommend termination of the study, the Data Safety Monitoring Board (DSMB) will be guided by a formal stopping rule based on the primary endpoint of incidence of DVT. The interim test statistics will be the primary outcome analysis for both safety and effectiveness. We will perform two formal interim analyses during the monitoring of the study (when 33% and 67% of the sample size has been achieved). The trial may be stopped for safety (*p* < 0.01) or effectiveness (*p* < 0.001). There will be no plans to terminate the trial for futility. We will account for alpha spending by the O’Brien Fleming method and the final *p* value will be considered at 0.048.

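### Sleeve length and device type exist only in the IPC arm, so listing them as intention-to-treat subgroups with interaction tests cannot work as written

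*Protocol article*

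**What the plan says.** The Subgroup analyses section restricts the subgroup comparisons of the primary outcome to the intention-to-treat cohort, uses a chi-square test with a risk ratio, and adds that "multivariable logistic regression will be used to report the results of tests of interactions" for the subgroups listed. Ten items follow. Eight are patient characteristics or the country. The last two are sleeve length (above-knee and below-knee, each against control) and device type (sequential "devices compared to control and non-sequential devices compared to control"). Table 1 gives only chi-square and relative risk for subgroup analyses and mentions no interaction test.

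On the devices themselves, Study design says "we permit the use of a broad array of IPC devices from various manufacturers intended for DVT prophylaxis" and that the type used is recorded. Nothing says that it is randomized, stratified, or fixed by site or before randomization. Under Intervention data the trial will "report the use of thigh- or knee-length sleeves and the use of foot pumps", and will also report why IPC was not used in the IPC group and why it was used in the control group. Study population keeps every enrolled patient in the intention-to-treat population whether or not the allocated intervention was received.

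**The concern.** A subgroup analysis compares the arms within a class of patients that can be identified in both arms. Sleeve length and device type do not meet that condition, because a control patient has neither. What the plan can actually compute is one part of the IPC arm, picked out by what was applied after randomization, against all controls. Three things follow. The promised interaction test does not exist for these items. The intention-to-treat label is wrong for them. Any difference in baseline risk between users of the two classes passes straight into the risk ratios.

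At stake is how these results will be read. A device-class contrast reported as a pre-specified intention-to-treat subgroup would carry a credibility that it cannot have.

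**Working it through.** **The plan's own figures.** The article gives no figure for these two items. "The PREVENT trial will enroll 2000 critically ill patients from 16 hospitals in 4 countries" supplies the site count and the total; 1:1 allocation is assumed here. For orientation, the overall sample size reproduces. With 7% vs 4%, 80% power and two-sided 5%:

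n = [1.960·√(2·0.055·0.945) + 0.842·√(0.07·0.93 + 0.04·0.96)]² / 0.03² = 906 per arm, or 971 per arm with continuity correction (1942 in total; 1966 at the final level of 0.048).

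This is consistent with 2000 and does not bear on the point.

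**1. Interaction.** Let T = 1 for IPC and 0 for control, and D = 1 for a sequential device. The model needs columns 1, T, D and T·D. Controls have no device, so D = 0 whenever T = 0. Hence T·D = D for every patient, and the matrix has rank 3 of 4. The most that can be estimated is a contrast between the device classes inside the IPC arm, which is not randomized. Controls who received IPC could carry a recorded type, but that is post-randomization crossover and gives no valid control subgroup. If each control is given the class that its site used, the rank is 4 of 4 and the interaction is estimable.

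**2. Intention-to-treat.** Study population keeps non-receivers in. Intervention data expects IPC-arm patients without IPC, and these have no sleeve and no device type. It also reports foot pumps separately from thigh- and knee-length sleeves, so a patient with foot pumps only fits neither sleeve class. Those patients drop out of the IPC side while all controls stay in.

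**3. Confounding, expected size.** Assume, beyond the documents, that half of the IPC patients use each class and that the places using them have control risks c1 and c2, pooled to 7%. Against all controls, the expected RR is (true RR)·c1/0.07 for the first class and (true RR)·c2/0.07 for the second.

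| True RR | c1 / c2 | RR, first class | RR, second class |
|---|---|---|---|
| 1 | 7% / 7% | 1.00 | 1.00 |
| 1 | 8% / 6% | 1.14 | 0.86 |
| 1 | 9% / 5% | 1.29 | 0.71 |
| 4/7 | 9% / 5% | 0.73 | 0.41 |

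The last row shows two equally effective classes that look different. The first row shows no bias when the risks are equal.

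**4. Confounding, false-positive rate.** Assumptions not in the documents: device follows site, 16 equal sites with 62 patients per arm, 8 sites per class, mean DVT risk held at 5.5% (midway between 7% and 4%), normally distributed site log-odds, no IPC effect. The test is an uncorrected chi-square at two-sided 5%. A rerun with 200,000 replicates gives:

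| Between-site SD of log-odds | Each class vs all controls | At least one of the pair | Each class vs same-site controls |
|---|---|---|---|
| 0 | 4.9% | 9.3% | 4.8% |
| 0.3 | 6.0% | 11.4% | 4.8% |
| 0.5 | 8.0% | 15.4% | 4.7% |
| 0.8 | 13.4% | 24.5% | 4.6% |

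The pair column must be read against its own baseline of about 9%, which is the effect of making two tests.

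**The case against.** A reader might infer that these comparisons are in fact confounded by site. The article does not support that. It permits many devices across 16 hospitals in 4 countries, and it says that country differences may influence baseline DVT risk. It does not say that a hospital or country uses one class. If hospitals mix classes, the site mechanism weakens or disappears.

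A reader might also choose a stark illustration: no IPC effect, sites at 10% and 4%, device perfectly aligned with risk. Then 20/500 vs 70/1000 gives RR 0.57 (p = 0.021) and 50/500 vs 70/1000 gives RR 1.43 (p = 0.043, or 0.055 with continuity correction). That is an assumed worst case. If 16 sites split 8 and 8 on risk and device were allotted to sites at random, perfect alignment would arise in 2 of 12,870 allocations. Nor does anything in the article plan a recommendation of one device class, so that consequence is speculative.

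Other points on this side are fair. These are the last two of ten items, the only two with no stated effect-modification rationale, and they are openly worded as each class against control. Table 1 names no interaction test, so the sentence on interactions may simply be loose drafting. A supplementary table that is not shown may say more. These points limit the weight of the matter, but they do not rescue the text: the section makes no exception for the two items, and it places them in the intention-to-treat cohort.

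**Conclusion.** The point holds in a bounded form. Two parts need no assumption beyond the article: the interaction test cannot be estimated for sleeve length or device type, and the comparisons are not intention-to-treat under the article's own definition. The Subgroup analyses section and Table 1 also disagree on whether interaction tests are planned, and should be reconciled.

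The third part is that the comparisons are non-randomized and open to confounding, with site or country a likely but undocumented source. Its size depends on between-site variation, for which the article gives no value. Over the assumed SDs of 0.3 to 0.8, with device following site, the error of each test rises from about 5% to between 6% and 13%. The chance that at least one of the pair rejects rises from about 9% to between 11% and 24%. With mixed devices within sites, or equal risks, this inflation shrinks or vanishes.

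The primary comparison of all IPC with all control patients is not affected. The text should still be corrected, because a pre-specified analysis cannot be run as written.

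**What to change.** By default:

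- Remove sleeve length and device type from the intention-to-treat subgroup list and from the interaction tests.
- Present them as exploratory, non-randomized comparisons by device received. Compare with controls from the same sites, or adjust for center, and give no interaction p-value.
- State how IPC-arm patients without a device, and those with foot pumps only, are counted.
- Bring the Subgroup analyses section and Table 1 into agreement on interaction tests for the other eight items.

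Optionally, where sites mainly used one class, define the class at site level (or site and calendar period if a site changed device) and assign it to both arms. Compare all randomized patients within each class, and test arm-by-class with center as random effect.

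The cost is rewording, plus at most one variable derived from device data that are already recorded. The article describes recruitment as still open and the authors as blinded until database lock, so the change can precede unblinding. There are limits. Same-site controls do not remove selection by device within a site. The site-level version needs a majority rule for mixed-device sites. The contrast between classes stays observational either way.

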#### Sensitivity analyses

In a sensitivity analysis, we will consider all lower-extremity DVT and PE events as incident. In another sensitivity analysis, we will consider post-enrollment lower-extremity DVT and PE events if they occur on calendar day 2 or later post enrollment [13]. Because mortality can be a competing outcome with VTE, we plan a sensitivity analysis that is restricted to patients who survive and in the ICU for at least 14 days. Because baseline ultrasonography can be missing, some patients may have a positive non-baseline ultrasonography without a baseline ultrasonography examination, making it difficult to determine whether DVT was a prevelent or an incident event. In these patients, we will have a sensitivity analysis assuming that the missing baseline ultrasonography was negative for DVT and another analysis assuming that the exam was positive. We will examine dose-effect relationship by assessing the relationship of the IPC duration and incident proximal lower-extremity DVT (Table 1 and Additional file 2: SPIRIT 2013 Checklist).

**Table 1 Tab1:** Summary of analysis plan

Variables	Intention-to-treat cohort	Per Protocol cohort
Baseline characteristics	No statistical comparisons will be performed	None
Intervention and co-interventions	Chi-square, Fisher’s exact test, Mann-Whitney *U* test, *t* test as applicable	None
Primary outcome	1. Primary analysis: chi-square. Report relative risk. Generalized linear mixed model (GLMM) incorporating center/site as random effect. Report as adjusted relative risk. If a significant difference detected: relative risk reduction, absolute risk reduction and number needed to treat (or harm) will be reported 2. Secondary analyses: unadjusted Cox proportional analysis, Kaplan-Meier (KM) curves, adjusted Cox proportional analysis	1. Primary analysis: chi-square and relative risk. Generalized linear mixed model (GLMM) incorporating center/site as random effect. Report as adjusted relative risk. If a significant difference detected: relative risk reduction, absolute risk reduction and number needed to treat (or harm) will be reported. 2. Secondary analyses: unadjusted Cox proportional analysis, KM curves, adjusted Cox proportional analysis
Secondary outcomes	Chi-square. Report relative risk	None
Subgroup analyses	Chi-square. Report relative risk	None

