### Primary outcome

The primary outcome is incident proximal lower-extremity DVT detected after the third calendar day of enrollment during the intervention period (defined as the number of calendar days from enrollment until the end of the intervention period; that is, diagnosis of lower-extremity DVT, PE, ICU discharge, death, full mobility or 28 days). The primary outcome tests the primary hypothesis that IPC reduces incident proximal lower-extremity DVT (Additional file 1: Table S3).

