***Secondary outcomes related to lower-extremity DVT other than incident proximal lower-extremity DVT***
*Prevalent – proximal DVT.* DVT diagnosed on the first ultrasonography within the first three calendar study days are considered “prevalent,” (i.e. reflecting a baseline characteristic); however, some of these DVTs may have occurred after enrollment. While a narrower time window to perform the first ultrasonography would have been ideal, feasibility considerations (i.e. logistics of performing an ultrasonography by a certified technician) mandated a broader time window. Therefore, it is possible that the intervention may reduce prevalent proximal DVT*Distal DVT (incident + prevalent).* In general, we will not consider isolated distal lower-extremity DVT. Study surveillance ultrasonography does not include distal calf veins (i.e., peroneal, posterior, anterior tibial, and muscular veins). However, if diagnosed by the treating team, then we will document their occurrence. If lower-extremity DVT occurs in both proximal and distal veins, it will be counted as a proximal DVT
*All lower-extremity DVT (all proximal and distal)*
3.

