***Secondary outcomes related to PE***

*Incidence of PE*

*Extent of PE: unilateral, bilateral*
*PE with cardiopulmonary complications* (supraventricular arrhythmias, ventricular arrhythmias, hypotension (systolic blood pressure ≤ 80 mmHg or decrease of 30 mmHg from baseline) or increase in inotropic support ≥ 50% from pre-event, endotracheal intubation, cardiopulmonary arrest, pulmonary artery hypertension (pulmonary artery (PA) systolic ≥ 60 mmHg or death)
*Composite all lower-extremity DVT and PE*
4.

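### As worded, both sensitivity analyses of the day-3 cut-off also replace proximal DVT with lower-extremity DVT plus PE, so neither isolates the effect of the cut-off

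*Protocol article*

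**What the plan says.** The protocol article (Primary outcome) counts "incident proximal lower-extremity DVT detected after the third calendar day of enrollment during the intervention period". Two elements define the event: its type (proximal DVT) and its window (after calendar day 3).

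The cut-off separates incident from prevalent events. Under the secondary outcomes for other lower-extremity DVT, "DVT diagnosed on the first ultrasonography within the first three calendar study days are considered" prevalent. The same paragraph concedes that some of these clots may arise after enrollment and that IPC could reduce them.

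The section Sensitivity analyses then relaxes the cut-off twice:

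- No cut-off: "In a sensitivity analysis, we will consider all lower-extremity DVT and PE events as incident".
- Cut-off moved earlier: "we will consider post-enrollment lower-extremity DVT and PE events if they occur on calendar day 2 or later post enrollment".

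Elsewhere the article treats this wider event set as something other than the primary endpoint. Its secondary outcome for DVT at any leg site spells out that proximal and distal clots both count, and the PE group of secondary outcomes has its own entry, "Composite all lower-extremity DVT and PE".

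**The concern.** A sensitivity analysis of a cut-off is informative when only the cut-off moves. Here the cut-off deserves such a test. The baseline scan may come up to 48 h after enrollment, and the article itself accepts that IPC might act on clots that the day-3 rule labels prevalent. The primary outcome may therefore leave out events that the intervention affects.

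As worded, both analyses move the window and also enlarge the event set. If the resulting RR differs from the primary RR, a reader cannot tell from that analysis whether early proximal DVT or the added distal DVT and PE caused the difference. If it agrees, the agreement may come from two opposite shifts.

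The added events also reach the data by another route. Proximal veins are scanned twice weekly and read by blinded radiologists. For distal veins, "Study surveillance ultrasonography does not include distal calf veins", so a distal clot counts only when the unblinded treating team happens to diagnose it. The scanning schedule described under Study design contains no PE imaging.

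**Working it through.** **Step 1. The definitions side by side.**

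| Analysis | Window | Event set |
|---|---|---|
| Primary outcome | after calendar day 3 | proximal lower-extremity DVT |
| Sensitivity 1 | no cut-off | all lower-extremity DVT and PE |
| Sensitivity 2 | calendar day 2 onward | lower-extremity DVT and PE |

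Both columns change in both sensitivity rows. The remaining analyses in that section do not fill the gap. The missing-baseline pair concerns only patients with a later positive scan and no baseline scan, the 14-day analysis restricts the patients, and the dose-effect analysis concerns IPC duration. No listed analysis changes the window alone.

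**Step 2. The plan's own figure.** Inputs: 7% vs 4% and 80% power (Abstract), 2000 patients (Study design), two-sided 5% (Statistical analysis). Equal allocation is assumed, as the article does not state the ratio. With mean rate 0.055 and difference 0.03:

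n per arm = [1.960·√(2·0.055·0.945) + 0.842·√(0.07·0.93 + 0.04·0.96)]² / 0.03² ≈ 905.3, rounded up to 906, or 1812 in total. With continuity correction the total is 1942 (1966 at the final alpha of 0.048). The 2000 patients are consistent with this. The figure serves only to fix 7% and 4% as base rates; the point does not depend on it.

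**Step 3. Widen the event set only (illustration).** The article gives no rate for distal DVT or PE. Assume that k percentage points of events unaffected by IPC are added to each arm and keep the day-3 window. Then RR = (4 + k)/(7 + k):

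- k = 0: 4/7 = 0.571
- k = 1: 5/8 = 0.625
- k = 2: 6/9 = 0.667
- k = 3: 7/10 = 0.700

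**Step 4. Change the window only.** Keep proximal DVT, drop the cut-off, and assume e points of early proximal DVT unaffected by IPC in each arm. Then RR = (4 + e)/(7 + e), the same formula, so e = 1, 2 or 3 gives 0.625, 0.667 or 0.700. The two causes leave the same trace.

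**Step 5. Change both.**

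- *Added together.* e = 2 and k = 2, both unaffected: (4 + 2 + 2)/(7 + 2 + 2) = 8/11 = 0.727. The RR alone does not show how much of the move belongs to the window.
- *Window harmless.* Early DVT has the same RR as the primary outcome, with 2 points in control and 2·4/7 = 1.143 with IPC. Proximal DVT without a cut-off stays at 5.143/9 = 0.571. Adding 2 unaffected points of distal DVT or PE gives 7.143/11 = 0.649, a shift caused wholly by the wider event set.
- *Offsetting.* Two points of unaffected early DVT, plus added events at 2% in control and 0.5% with IPC: (4 + 2 + 0.5)/(7 + 2 + 2) = 6.5/11 = 0.591. This looks close to 0.571, although dropping the cut-off alone would give 6/9 = 0.667.

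**Step 6. What the secondary outcomes can recover.** Prevalent proximal DVT is compared between arms. Scanning stops at the first lower-extremity DVT, so incident and prevalent proximal counts per arm can largely be added to give all proximal DVT. The prevalent count merges calendar days 1 to 3, so that sum cannot be split to start at day 2.

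**The case against.** The best counter-argument is that the sentences only reclassify events. They say which events count as incident once the split is removed or moved, after which proximal DVT and PE would each be re-analysed on their own. The article uses the word composite where it pools, and that word is absent here. This reading is possible. The text does not state it, though, and the phrase chosen for the first analysis matches the label that the article elsewhere gives to proximal plus distal DVT. If separate re-analysis is meant, one clause would say so.

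A reader might go further than the point made here and infer that the plan cannot show whether the result depends on the cut-off, or that the matter of early DVT labelled prevalent stays wholly unanswered. The article does not support that:

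- Prevalent proximal DVT is a secondary outcome, reported with RR and 95% CI, so an early IPC effect is looked at directly.
- Distal DVT and PE are each secondary outcomes, so a reader can see roughly what they contribute.
- The section Diagnostic testing compares VTE testing between arms to detect unequal ascertainment.
- Isolated distal DVT is in general not considered, and distal clots found with proximal ones count as proximal, so the distal addition may be small.

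These four points stand and limit the concern. They do not supply a prespecified analysis that moves only the window, and they give nothing for the day-2 version.

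Two further objections deserve a reply. The added rates are assumed; that is so, and they show only that the two causes can be confused. The loss of power from adding unaffected events is no argument, because sensitivity analyses are not powered tests. Finally, the supplementary tables are not at hand. If they restrict both analyses to proximal DVT, the wording of the article still needs to be brought into line.

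**Conclusion.** The point holds in a limited form. On the plain wording, both sensitivity analyses of the day-3 cut-off change the window and the event set together, so neither isolates the cut-off. Part of the answer can be pieced together from secondary outcomes, but that is not prespecified and leaves out the day-2 variant.

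The size is unknown, because the article gives no rates for early DVT, distal DVT or PE. Under the assumption of 1 to 3 added points per arm that IPC does not affect, the RR moves from 0.57 to 0.63–0.70 with no change of window; with few added events the shift would be small. The conclusion rests on the definitions and not on these figures. It concerns supportive analyses only and is minor: the primary test, the sample size and the control of type I error are untouched.

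**What to change.** Reword the two analyses under Sensitivity analyses so that the event stays proximal lower-extremity DVT and only the window moves:

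1. all proximal lower-extremity DVT from enrollment, with no cut-off;
2. proximal lower-extremity DVT from calendar day 2 onward.

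Use the same population, chi-square test and RR with 95% CI as for the primary outcome. Report any version that adds distal DVT or PE separately and label it as an analysis of a different endpoint. If the intention was to re-run proximal DVT and PE separately, say so in one clause.

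The cost is a few lines of text, agreed before the database is locked and the steering committee sees results by group. The outcome data are already being collected, and the broader DVT-plus-PE composite remains as a secondary outcome, so nothing is lost.

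### The dose-effect analysis does not fix its IPC exposure; read as cumulative time, the exposure depends on the outcome and on time at risk, and can show a false association in either direction.

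*Protocol article*

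**What the plan says.** The last item under Sensitivity analyses reads: "We will examine dose-effect relationship by assessing the relationship of the IPC duration and incident proximal lower-extremity DVT". That is the whole specification. Metric, exposure window, analysis set and model are not given, and Table 1 has no row for it.

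Four other statements in the article bear on what the exposure could be:

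- Primary outcome counts only "incident proximal lower-extremity DVT detected after the third calendar day of enrollment during the intervention period", and that period closes at "diagnosis of lower-extremity DVT, PE, ICU discharge, death, full mobility or 28 days". The outcome itself is therefore one of the events that end the period.
- Study design describes the intervention differently: "The study intervention will continue for the duration of the ICU stay or up to 28 days after randomization". DVT is not named there as an end of IPC. It is named as an end of ultrasound surveillance, which runs "twice weekly thereafter until the diagnosis of a lower-extremity DVT or PE, ICU discharge, death, full mobility or 28 days".
- Intervention data describes one on-study measure of use, the "average daily duration of use (excluding study first and last days because they are usually less than 24 h".
- Study design sets the daily target: "IPC will be applied continuously for at least 18 h per day".

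**The concern.** A dose-effect analysis needs an exposure that is settled before the outcome occurs. Cumulative IPC time is not, for two reasons that act in opposite directions.

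- **Truncation.** If time is counted to the end of the intervention period as Primary outcome defines it, a patient with DVT stops accumulating IPC because of the DVT. The longest durations then belong largely to patients who stayed DVT-free, and long IPC looks protective.
- **Time at risk.** A patient who leaves by day 3 has a short duration and cannot have the outcome. A patient who stays four weeks has many more days in which DVT can arise and be scanned for. Long IPC then looks harmful.

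The result would reflect the balance of these two mechanisms as much as any effect of IPC. A gradient tends to be read as evidence on causation, so a false one in either direction would mislead.

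**Working it through.** **The plan's own figures.** The article gives no figure for this analysis. Its design figure (7% v 4%, 80% power) reproduces: with a two-sided alpha of 0.05 and 1:1 allocation assumed, n per arm = [1.96·√(2·0.055·0.945) + 0.842·√(0.07·0.93 + 0.04·0.96)]² / 0.03² = 906, and 1000 per arm gives 83.8% power. It matters here only as the source of two inputs: about 1000 IPC patients (half of 2000) and a 4% DVT rate.

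**Which exposure is meant.** Where the article means a daily rate it says so, under Intervention data. Elsewhere a plain duration means length of use: IPC before randomization, therapeutic anticoagulation, compression stockings. The dose-effect sentence uses the plain form, so cumulative time is the natural reading, though the text does not settle it.

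**Time at risk, by hand.** Take a constant daily DVT hazard h after day 3 and no IPC effect. With h = 0.0058 (the value giving about 4% overall in the 10-day-stay scenario below), risk by length of stay is 1 − (1 − h)^(stay − 3):

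- stay 3 days: 0
- stay 10 days: 1 − 0.9942^7 = 4.0%
- stay 28 days: 1 − 0.9942^25 = 13.5%

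Risk rises with stay although IPC does nothing. Truncation works against this: a patient destined to stay 28 days whose DVT is found on day 11 is recorded with 11 IPC days.

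**Null simulation, duration truncated at DVT.** From the documents: 1000 patients, about 4% DVT, DVT possible only after day 3, twice-weekly scans (placed on days 4, 7, 11, 14, 18, 21, 25 and 28), and IPC days cut at DVT detection, ICU discharge or day 28. Assumed, because the article gives neither: exponential ICU stay with the scale shown, and hazard shape. Each cell is the odds ratio for DVT per 7 IPC days from logistic regression, with the share of 300 replicates significant at 5%.

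| ICU stay scale | Constant hazard | Hazard half-life 7 d | Hazard half-life 3 d |
|---|---|---|---|
| 6 d | 1.81 (95% false harm) | 1.38 (46% false harm) | 1.10 (1% false harm) |
| 10 d | 1.29 (42% false harm) | 0.95 (0%) | 0.73 (35% false protection) |
| 14 d | 1.10 (7% false harm) | 0.80 (29% false protection) | 0.60 (98% false protection) |
| 20 d | 0.95 (2% false protection) | 0.69 (94% false protection) | 0.51 (100% false protection) |
| 30 d | 0.81 (42% false protection) | 0.59 (100% false protection) | 0.44 (100% false protection) |

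At 7% DVT, 6-day scale and constant hazard, the odds ratio is 1.91.

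**Duration following ICU stay.** A further null simulation at 4% DVT, under its own assumed stays and hazard shapes, gave 0.35 to 1.22 with truncation at DVT and 1.39 to 2.43 when duration follows ICU stay, as Study design describes. On the second reading every value lies above 1.

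**Average daily hours.** With daily hours drawn at mean 20, SD 2.5, independently of outcome (constant-hazard runs), the odds ratio per hour was 0.999 to 1.007 and rejection 3% to 7%. The Monte Carlo standard error at 5% is √(0.05·0.95/300) = 1.3 percentage points, so this is compatible with the nominal level. Independence is built in, so the run shows that averaging creates no truncation artefact. It does not show that average hours are unconfounded.

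**The case against.** The best defence is that the flawed exposure is not written down. The sentence says duration, not total duration, and the only on-study measure the article describes is the daily average, which escapes the artefact. The supplementary tables and the published protocol, not shown here, may define it. This is also one exploratory item that bears on neither the primary test, the sample size nor the stopping rule.

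Part of this stands. A reader might infer that the plan commits to total IPC time; it does not, and the point is conditional on the cumulative reading. A reader might also infer that IPC always ends at DVT; that rests on Primary outcome alone, and Study design says otherwise. And a reader might infer that the artefact will favour IPC and be taken as confirming efficacy. The documents do not support that: the sign depends on ICU stay and hazard shape, which they do not give, and nothing in them says the result will be presented as causal evidence or used to prolong IPC.

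What does not stand is that this is merely omitted detail. The article presents itself as the statistical analysis plan, and its one sentence names an exposure whose ordinary reading is invalid under either section's account of when IPC ends.

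**Conclusion.** The point holds in conditional form. The exposure metric and window are not fixed, and the natural reading allows a dose that is partly determined by the outcome or includes time after it, and that tracks time at risk. With no IPC effect, the odds ratio per 7 IPC days can lie anywhere from well below 1 (0.35) to above 2 (2.43), with false-positive rates up to 100% in the truncated simulations. These sizes rest on assumed ICU stays and hazard shapes and are not predictions for this trial. In some scenarios the two mechanisms nearly cancel (0.95 at a 20-day scale with constant hazard). That the distortion exists follows from the article's own definitions; its sign and size do not. It is worth correcting before analysis, but it concerns a sensitivity analysis and leaves the primary comparison untouched.

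**What to change.** In the dose-effect sentence under Sensitivity analyses, replace the IPC duration with exposure measured before the event, choosing one of:

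- a Cox model within the IPC arm, with patients at risk from day 4 and time-updated average daily IPC hours up to the previous day, adjusted for the covariates already listed under Analysis of primary outcome; or
- a day-4 landmark relating mean daily IPC hours on days 1–3 to DVT from day 4 onward, among patients still at risk.

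State that cumulative duration to the end of the intervention period will not be used. Reconcile Study design and Primary outcome on when the intervention period ends. Label the analysis observational, since confounding by the reasons for non-use remains under either option.

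The cost is a change of wording and slightly more analysis work. Cox models for DVT are already planned, and the daily average under Intervention data implies that use is recorded by day. The landmark option is simpler but uses only three days of exposure.
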